## Abstract

**Background:**

Pregnancy offers a unique opportunity to identify women at higher future risk of type 2 diabetes mellitus (DM). In pregnancy, a woman has greater engagement with the healthcare system, and certain conditions are more apt to manifest, such as gestational DM (GDM) that are important markers for future DM risk. This study protocol describes the development and validation of a risk prediction model (RPM) for estimating a woman’s 5-year risk of developing type 2 DM after pregnancy.

**Methods:**

Data will be obtained from existing Ontario population-based administrative datasets. The derivation cohort will consist of all women who gave birth in Ontario, Canada between April 2006 and March 2014. Pre-specified predictors will include socio-demographic factors (age at delivery, ethnicity), maternal clinical factors (e.g., body mass index), pregnancy-related events (gestational DM, hypertensive disorders of pregnancy), and newborn factors (birthweight percentile). Incident type 2 DM will be identified by linkage to the Ontario Diabetes Database. Weibull accelerated failure time models will be developed to predict 5-year risk of type 2 DM. Measures of predictive accuracy (Nagelkerke’s *R*^2^), discrimination (C-statistics), and calibration plots will be generated. Internal validation will be conducted using a bootstrapping approach in 500 samples with replacement, and an optimism-corrected C-statistic will be calculated. External validation of the RPM will be conducted by applying the model in a large population-based pregnancy cohort in Alberta, and estimating the above measures of model performance. The model will be re-calibrated by adjusting baseline hazards and coefficients where appropriate.

**Discussion:**

The derived RPM may help identify women at high risk of developing DM in a 5-year period after pregnancy, thus facilitate lifestyle changes for women at higher risk, as well as more frequent screening for type 2 DM after pregnancy.

## Background

Type 2 diabetes mellitus (DM) is a serious metabolic condition that affects over 400 million people and accounted for 1.6 million deaths worldwide in 2016 [1]. DM and its complications are major contributors to reductions in life expectancy and quality of life [2–4]. Costs to healthcare systems attributed to DM are substantial with estimated annual global costs of US$1.3 trillion or 1.8% of global gross domestic product [5]. These costs are expected to rise further with growing type 2 DM prevalence. Some of the highest increases in DM prevalence have occurred among young women [6, 7]. Developing type 2 DM at younger ages is associated with worse morbidity and mortality compared to developing the condition at older ages [8]. Identifying opportunities for reversing the rising prevalence in young women is therefore essential to reducing the burden of DM.

Pregnancy provides a unique opportunity for estimating future type 2 DM risk, and then implementing potentially risk reducing strategies. Due to the intense physiological demands of pregnancy, some women develop temporary conditions such as GDM and hypertensive disorders of pregnancy that are important markers for future DM risk [9, 10]. GDM occurs in 5 to 20% of pregnancies and is associated with a seven-fold increased risk of type 2 DM [9–12]. Pregnancy is also a time when women are more engaged with the healthcare system and may be more motivated to implement behavioral changes to improve their health for the sake of their family.

Despite strong evidence among non-pregnant, high-risk populations that type 2 DM can be prevented with lifestyle modifications [13, 14], there remains limited post-partum follow-up relating to DM risk among women at high risk of developing DM [15]. Evidence also suggests that many women with GDM perceive their 10-year risk of developing DM to be low [16, 17]. Yet, 10–40% of women with GDM progress to DM within the first 5 years after delivery [18–20], underscoring the need for better risk communication.

A risk prediction model (RPM) for estimating future DM risk following delivery will facilitate risk communication and will support clinicians to identify women at high risk who might benefit from preventative interventions. Existing DM RPMs currently include only a small number of pregnant women and do not include important predictors of DM that develop during pregnancy [21–26]. Models developed among postpartum women are limited to women with a previous history of GDM [27–29]. These models would not be applicable to women who do not develop GDM during pregnancy but who may still be at high risk of future DM. Furthermore, each of these models were derived in small samples (*N* = ≤ 395) with limited ethnic variation.

To address the need for a population-based DM RPM that may be applied to all postpartum women, we propose the development and validation of a novel model using unique administrative datasets that capture all births within the population covered under a single-payer health system for over 200,000 deliveries.

## Methods

### Data sources

The RPM will be derived and validated using population-based administrative data collected in Ontario, Canada. These datasets are held at ICES, an independent, non-profit research institute whose legal status under Ontario’s health information privacy law allows it to collect and analyze health care and demographic data, without consent, for health system evaluation and improvement. The datasets are linked using unique encoded identifiers and analyzed at ICES.

The major source of data for this project will be Ontario’s perinatal registry, the Better Outcomes Registry and Network (BORN). This dataset was established in 2009 and captures information from hospitals, midwifery practice groups, specialized antenatal clinics, prenatal screening laboratories, and fertility clinics for all deliveries occurring within hospitals in Ontario. Data quality of BORN data elements was recently assessed and was found to have good agreement with data from patient charts [30]. Of the 29 data elements assessed, 23 elements had greater than 90% agreement, including maternal weight and height. Prior to BORN, pre- and peri-natal data were collated in the Niday database, now known as the BORN legacy data [31]. This earlier database was first created in 1997 and by 2008 captured data for 96% of deliveries in Ontario. While data quality for Niday data is lower, the percentage agreement between Niday and patient chart for important predictors including infant birthweight and gestational age at delivery exceed 90% [31]. Data collated in both databases include maternal demographic, behavioral, and health status characteristics. Obstetric complications and delivery outcomes are also captured. BORN is funded by the Ontario Ministry of Health and Long Term Care and administered by The Children’s Hospital of Eastern Ontario. Since the administrative data do not capture information on ethnicity, maternal ethnicity will be ascertained using a validated algorithm which uses surnames to assign an ethnicity (South Asians, Chinese, Other) to all residents of Ontario [32]. Linkage to the Ontario Laboratories Information System (OLIS) will be used to capture 50 g oral glucose challenge test (OGCT) values. OLIS was established in 2006 and holds data relating to medical laboratory test orders and results from community, hospital and public laboratories across Ontario. The OGCT is used to screen for GDM, is currently offered to all pregnant women and is typically administered between 24 and 28 weeks’ gestation [33]. Data relating to comorbidities such as cardiovascular disease and prior pregnancy history will be obtained from the Discharge Abstract Database (DAD). This database captures detailed clinical and administrative data for hospital admissions and day surgeries in Ontario.

To obtain outcome data, we will use the Ontario Diabetes Database (ODD). This database was established in 1991 and contains all individuals with DM in Ontario. This database captures data from hospital discharge abstracts, Ontario drug benefit claims and physician service claims and data from this database are currently available until 31st March 2019. The use of data in this project was authorized under section 45 of Ontario’s Personal Health Information Protection Act, which does not require review by a Research Ethics Board.

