### Main predictors

Table 1 lists the predictors and the pre-specified functional forms for each.

**Table 1 Tab1:** Pre-specification of predictors for risk prediction model

Variable type	Variable	Specification	df
Demographics	Age at index	Continuous variable	1
	Income quintile	Five categories	4
	Rurality	Binary: yes/no	1
	Immigrant status	Three categories (non-immigrant, previous (over 10 years ago), recent (10 years or less)	2
	Ethnicity	Three categories (South Asian, Chinese, Other)	2
Lifestyle	Pre-pregnancy BMI, kg/m^2^ (self-reported)	Continuous	1-3
Lifetime Health history	Previous mental health condition	Binary: yes/no	1
	Previous cardiovascular disease	Binary: yes/no	
Prior pregnancy history	Parity	Five categories (0, 1, 2, 3, > 3)	4
	Gravidity	Four categories (1, 2, 3, > 3)	3
	Previous GDM	Three categories: yes/no/NA	2
	Previous gestational hypertension or preeclampsia	Three categories: yes/no/NA	2
Index pregnancy	50 g oral glucose challenge test, mmol/L	Continuous	1-3
	GDM	Binary: yes/no	1
	Preeclampsia	Binary: yes/no	1
	Gestational hypertension	Binary: yes/no	1
	Caesarean-section	Three categories: planned/emergency/no	1
	Premature delivery	Binary: yes/no	1
Newborn	Birthweight	Continuous (for women with a multi-fetal birth, the child with the higher birthweight will be used)	1
	Large for gestational age (LGA) birthweight > 90th	Binary: yes/no (for women with a multi-fetal birth, any child with a record for LGA will be used)	1

Choice of the candidate predictors was informed by a systematic literature review, consultation with the project advisory board, clinicians, and the availability of the predictors within the study’s data sources. To enhance usability, predictors of the model were also chosen based on their likely availability to intended users of the model. Continuous variables with limited variation and binary variables with small counts will be excluded. While categorical variables have been pre-specified, frequency distributions will be examined and categories may be combined where there are small numbers. Interactions between all predictors and each of age, GDM and ethnicity will be considered for inclusion into the model due to expected differences in the effect of these predictors by the selected variables. Interactions which improve model fit will be included in the final model.

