### Model presentation

The final regression model and validation results will be published in full in a peer-reviewed journal and according to the TRIPOD guidelines. The regression formula will be subsequently incorporated into a web-based calculator and will be integrated into electronic healthcare records. By integrating a calculator into electronic healthcare records, general practitioners will be able to readily access the necessary input data to estimate diabetes risk in postpartum women.

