### External validation

We will externally validate the algorithm using data from a population-based pregnancy cohort from Alberta, the Alberta Vital Statistics–Birth database [47]. This database is populated by maternal, pregnancy, and neonatal data and is linked to hospital admissions records (Discharge Abstract Database), emergency room/outpatient clinic visits records (the Ambulatory Care Classification System (ACCS)), and physician office visit records (Fee-for-Service Claims (CLAIM)). Linkage to the Alberta Health Care Insurance Population registry provides demographic data including ethnicity and rurality. Diabetes will be ascertained using ICD-9 and ICD-10 codes in hospitalization, ACCS, or CLAIM records. The RPM will be applied in this cohort to estimate 5-year risk of RPM in this external population. The predictive performance of the RPM will be assessed by estimating the previously described measures of calibration and discrimination. Where appropriate, the RPM model will be re-calibrated by adjusting the baseline hazard and the mean values of the predictors to that of the external validation cohort [48].

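### Mental health, cardiovascular and gravidity predictors are described as hospital-sourced but defined without that limit, so their coefficients may not fit what users of the tool will enter

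*Protocol article*

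**What the plan says.** The Data sources section states the source: "Data relating to comorbidities such as cardiovascular disease and prior pregnancy history will be obtained from the Discharge Abstract Database (DAD". It then gives that database's scope: "This database captures detailed clinical and administrative data for hospital admissions and day surgeries in Ontario". Cardiovascular disease is named as the example of a comorbidity; mental health is covered only by implication.

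Table 1 (Main predictors) lists "Previous mental health condition" and "Previous cardiovascular disease" as yes/no items under a lifetime-history heading. It lists gravidity as "Four categories (1, 2, 3, > 3". None of the three is restricted to hospital-treated events.

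On use, Main predictors says that "predictors of the model were also chosen based on their likely availability to intended users of the model". Model presentation expects that, once the calculator sits in electronic records, "general practitioners will be able to readily access the necessary input data to estimate diabetes risk in postpartum women". The Discussion adds a web calculator that women complete for themselves.

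For external validation, the Alberta cohort is linked to hospital and ambulatory records and to "physician office visit records (Fee-for-Service Claims (CLAIM" data. The article says how diabetes will be identified from these sources but not how the comorbidity predictors will be.

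**The concern.** The named source cannot deliver the variable that Table 1 describes. A mental health or cardiovascular condition treated only by a family physician or clinic leaves no trace in an admissions and day-surgery file. Neither does a pregnancy loss managed without admission. The woman is coded no, or the pregnancy is not counted. This applies even to a lifelong Ontario resident with full coverage.

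The coefficient then compares women treated in hospital with a reference group that contains the community-managed cases. At deployment, a general practitioner or the woman will probably answer yes for any such condition. If hospital-treated illness carries more diabetes risk than community-managed illness, women in the second group receive too high a 5-year risk.

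The planned safeguards would not clearly show this. Multiple imputation acts on missing values, and these are recorded as no. The bootstrap reuses the same coding. The missing-data and limitations text does not mention the issue.

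**Working it through.** **Set side by side**

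| Stage | What the predictor would capture |
|---|---|
| Ontario derivation (Data sources) | history seen in admissions and day surgeries |
| Table 1 definition | lifetime yes/no, no setting given |
| Deployment (Model presentation, Discussion) | general-practice record or self-report |
| Alberta validation | not stated; office-visit and ambulatory data available |

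The article handles its outcome differently. Diabetes may be identified from a hospital record, from two physician claims within a year, or from a drug record. Community care is therefore used to find a chronic condition as an outcome, but not, as written, as a predictor.

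**Illustration of size.** The plan has no figure of its own on this point to reproduce. All inputs below are assumptions, for one binary predictor, unadjusted, with no false positives in the hospital data:
- *P*, share of women with the lifetime condition: 0.10 to 0.30
- *f*, share of those ever admitted for it: 0.05 to 0.25
- *Rh* and *Rc*, diabetes rate ratios against unaffected women for admitted and non-admitted cases: (2.0, 1.2), (1.8, 1.3) and (1.5, 1.5)

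The model's prediction for a yes is the rate among admitted women, *Rh* times the unaffected rate. The true mean rate among all women with the condition is *f·Rh* + (1 − *f*)·*Rc*. Hence

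predicted/true = *Rh* / [*f·Rh* + (1 − *f*)·*Rc*]

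| *Rh*, *Rc* | *f* = 0.05 | *f* = 0.25 |
|---|---|---|
| 2.0, 1.2 | 2.0/1.24 = 1.61 | 2.0/1.40 = 1.43 |
| 1.8, 1.3 | 1.8/1.325 = 1.36 | 1.8/1.425 = 1.26 |
| 1.5, 1.5 | 1.00 | 1.00 |

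For a woman whose condition was managed wholly in the community, the ratio is *Rh/Rc*: 2.0/1.2 = 1.67, or 1.8/1.3 = 1.38.

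**Reference group.** Missed cases raise the rate among women coded no by the factor

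[(1 − *P*) + *P*(1 − *f*)·*Rc*] / [(1 − *P*) + *P*(1 − *f*)]

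With equal risks of 1.5:
- *P* = 0.10, *f* = 0.25: 1.0125/0.975 = 1.04
- *P* = 0.30, *f* = 0.05: 1.1275/0.985 = 1.14

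So with equal risks the yes group is predicted correctly, the no group is 4 to 14% too high, and the fitted ratio falls from 1.5 to between 1.5/1.04 = 1.44 and 1.5/1.14 = 1.31. For an uncommon condition the effect is negligible. At 1% prevalence and equal risks, a true ratio of 2.0 is estimated as 1.98 to 2.00 when the hospital data find 10 to 90% of cases; at 15% prevalence it is 1.76 to 1.97.

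**Absolute scale.** The Sample size section gives 2294 events in 756,956 person-years, or 0.00303 per person-year. At a constant rate, 5-year risk is 1 − exp(−5 × 0.00303) = 1.5%. At risks this low, rate ratios and risk ratios nearly coincide. If the affected group's true mean risk were 1.5%, the tool would show 1.5 × 1.26 = 1.9% to 1.5 × 1.61 = 2.4%.

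**Gravidity.** Uncounted losses put some women in too low a category in the derivation data, while a user would enter the full count. The documents allow no estimate of the effect or its direction.

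**The case against.** The article is a condensed account and says that variable definitions have been pre-specified, so a fuller document may name more sources. The perinatal registry is described as the major data source and as holding health-status information. This is a fair caution, strongest for mental health, which the source sentence does not name. It does not remove the point: the article assigns comorbidities and prior pregnancy history to one database, states that database's limits, and names no wider source for them.

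Harm also depends on several steps. The predictors must survive the exclusion of binary variables with small counts and the step-down to a simpler model, and a rarely coded hospital-only indicator could be dropped at either. Risk must differ by care setting, which the documents do not show. The calculator's wording is not fixed, and its development is to draw on a qualitative study. A broader Alberta definition might expose the mismatch. The Abstract also allows coefficients to be re-calibrated, although the External validation section mentions only the baseline hazard and predictor means. All of this stands, and it makes the harm possible and not certain.

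A reader might infer that the whole prior-pregnancy block is compromised. The documents do not support that. Parity, previous gestational diabetes and previous hypertensive disorders follow mainly from earlier deliveries, and in-hospital deliveries generate admissions. Nor do the documents say that gravidity will be built by counting admissions.

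**Conclusion.** The point holds in limited form. As written, the source of the cardiovascular predictor, of gravidity and, by implication, of the mental health predictor is narrower than their definition in Table 1 and narrower than what users are likely to supply. Imputation and internal validation would not reveal this.

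If the comorbidity predictors are retained and hospital-treated illness carries more risk, the model may over-predict for women with community-managed conditions. The 1.26 to 1.61-fold range rests wholly on the assumed rate ratios and admission shares. With equal risks there is no over-prediction among women entered as yes, only a modest rise in the reference rate where the condition is common. A reader might conclude that the calculator is bound to give wrong risks. The documents do not support this, because they give neither the severity difference nor the final predictor set.

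**What to change.** Define previous mental health condition and previous cardiovascular disease in Ontario from the Discharge Abstract Database plus physician service claims, and use the same code lists and source types in Alberta. Use the perinatal registry's obstetric fields for gravidity if they are recorded; the article does not confirm that they are, and it rates the older registry's data quality as lower.

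If claims cannot be used, label the items as hospital-treated history in Table 1, the published equation and the calculator, so that users enter the quantity the coefficient was estimated on. Add the restriction to the limitations.

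The cost is modest before model fitting: revised definitions and possibly one further linkage, since the article shows claims only as an input to the diabetes database and not as a predictor source. The drawback is that claims codes are less specific than hospital codes. The labelling option needs no new data.

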### Participants

The derivation cohort will consist of all women aged between 16 and 50 years (at index pregnancy) whose pregnancy resulted in a live birth or still birth in Ontario between 1st April 2006 and 31st March 2014. No minimum duration of pregnancy was required for inclusion into the derivation cohort. For women who had multiple pregnancies during this period, the first pregnancy occurring during the accrual window will be selected. The influence of this choice of pregnancy will be examined in sensitivity analyses involving the development and validation of models in separate cohorts containing a randomized choice of pregnancy. Women with pre-pregnancy DM as ascertained using the ODD and available variables in BORN indicating pre-existing DM will be excluded from the derivation cohort. Women who were ineligible for the Ontario Health Insurance Plan or were a non-Ontario resident in the 2 years prior to index date will be excluded since predictor and outcome data for these women will be incomplete. Index date is defined as 6 months post-partum. Women who had a second pregnancy prior to the index date and women who died prior to index will also be excluded.

### Main predictors

Table 1 lists the predictors and the pre-specified functional forms for each.

**Table 1 Tab1:** Pre-specification of predictors for risk prediction model

Variable type	Variable	Specification	df
Demographics	Age at index	Continuous variable	1
	Income quintile	Five categories	4
	Rurality	Binary: yes/no	1
	Immigrant status	Three categories (non-immigrant, previous (over 10 years ago), recent (10 years or less)	2
	Ethnicity	Three categories (South Asian, Chinese, Other)	2
Lifestyle	Pre-pregnancy BMI, kg/m^2^ (self-reported)	Continuous	1-3
Lifetime Health history	Previous mental health condition	Binary: yes/no	1
	Previous cardiovascular disease	Binary: yes/no	
Prior pregnancy history	Parity	Five categories (0, 1, 2, 3, > 3)	4
	Gravidity	Four categories (1, 2, 3, > 3)	3
	Previous GDM	Three categories: yes/no/NA	2
	Previous gestational hypertension or preeclampsia	Three categories: yes/no/NA	2
Index pregnancy	50 g oral glucose challenge test, mmol/L	Continuous	1-3
	GDM	Binary: yes/no	1
	Preeclampsia	Binary: yes/no	1
	Gestational hypertension	Binary: yes/no	1
	Caesarean-section	Three categories: planned/emergency/no	1
	Premature delivery	Binary: yes/no	1
Newborn	Birthweight	Continuous (for women with a multi-fetal birth, the child with the higher birthweight will be used)	1
	Large for gestational age (LGA) birthweight > 90th	Binary: yes/no (for women with a multi-fetal birth, any child with a record for LGA will be used)	1

Choice of the candidate predictors was informed by a systematic literature review, consultation with the project advisory board, clinicians, and the availability of the predictors within the study’s data sources. To enhance usability, predictors of the model were also chosen based on their likely availability to intended users of the model. Continuous variables with limited variation and binary variables with small counts will be excluded. While categorical variables have been pre-specified, frequency distributions will be examined and categories may be combined where there are small numbers. Interactions between all predictors and each of age, GDM and ethnicity will be considered for inclusion into the model due to expected differences in the effect of these predictors by the selected variables. Interactions which improve model fit will be included in the final model.

